#### Primary analysis

Comparisons of outcomes between the intervention and control groups will be made by appropriately adjusting for the correlation that occurs within general practices. Several common approaches for analysing data from CRCTs include: adjustment of standard statistical tests; analysis at the cluster level; and advanced statistical modelling techniques that can use both data recorded at the individual and cluster level. Modelling techniques are attractive since potential confounding variables at the patient, GP, and general practice level can be adjusted for. This is especially useful in CRCTs since the chance of baseline imbalance in prognostic factors is likely to be higher than in trials where individuals are randomised, because the number of clusters is generally fewer than the number of individuals.

Two common types of modelling are marginal and cluster-specific. In a cluster-specific approach the dependence between observations within a cluster is explicitly modelled, while in a marginal model this dependence is treated as a nuisance parameter. No consensus exists on which method is preferred, and both methods have advantages and disadvantages [48]. However, we plan to use marginal modelling using generalised estimating equations (GEEs). This modelling method has been chosen above a cluster-specific approach primarily for the following reasons. First, the cluster-specific random effects models that have been developed for non-normally distributed data present considerable computational difficulties which can result in biased estimates [29]. Second, the interpretation of the estimated regression coefficients from a GEE have a population interpretation, the same as that of regression coefficients from general linear models [49,50]. They measure the expected change in a response for those in the intervention group, as compared to those in the control group [51]. For cluster-specific models, the interpretation is conditional on the cluster. Neuhaus [52] suggested that interpretation of the intervention effect estimated from cluster-specific models in a CRCT is difficult because all participants within a cluster receive the same intervention. Because of this, Neuhuas remarked that marginal models are conceptually preferable for estimating cluster-level effects such as intervention status.

A disadvantage of using GEEs is that only one level of clustering can be modelled. This CRCT includes three levels of data: general practices; GP participants; and patient participants. It is possible to allow for clustering at the general practice level or the GP level. We have chosen to cluster at the general practice level because this is the unit of randomisation, and adjusting for clustering at this level will appropriately account for correlation that may occur between GPs within the same practice.

For both continuous and binary outcomes, we plan to fit GEEs with an exchangeable correlation structure, where responses from the same cluster are assumed to be equally correlated [53]. Additionally, we intend to use robust variance estimation that will provide valid standard errors even if the within-cluster correlation structure has been incorrectly specified [29,54]. For binary outcomes, a logit link function will be used.

Our primary analysis of outcomes will include adjustment for stratification variables (number of GPs per practice and rurality) and pre-specified potential confounders (available in the full version of the protocol). All pre-specified confounders will be included in the models even when no baseline imbalance exists. This approach has been chosen because confounder selection strategies that are based on collected data, (*e.g*., selecting confounders using preliminary statistical tests) result in models with poor statistical properties such as incorrect type I error rates [55-57]. In addition, for continuous outcomes that are collected at both baseline and follow-up (measurement of behavioural constructs and FAB-Q at the GP level), we will include the baseline measure as a covariate in the model. This method will appropriately adjust for any baseline imbalance that we may observe, and provides the most powerful analysis [57,58].

The potential confounders have been selected through discussion with LBP and implementation researchers, and from published research. For statistical parsimony, the number of included confounders for each outcome has been limited to those which we surmise are the most important. However, we will investigate the impact of additional confounders through modelling as part of the exploratory analyses (details available in the full version of the protocol). Additionally, estimates of intervention effect estimated from models including only the stratification variables will be presented.

Estimates of intervention effect from these models will yield odds ratios. For interpretability, we plan to also provide estimates of risk ratios using a simple formula that will utilise the odds ratios estimated from these models [59]. For each outcome, the estimate of intervention effect and its 95% confidence interval will be provided. For the primary outcomes we plan to provide estimates of the coefficient of ICC and their 95% confidence intervals.

No adjustment will be made for multiple testing. All tests will be two-sided and carried out at the 5% level of significance.

Any future change to the statistical methods outlined in this analysis strategy will be documented with full justification as an amendment to the full protocol.

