### Sample size

The primary process and patient outcomes are x-ray referral and LBP-specific disability as measured by the RDQ [37]. In the calculation of sample size for these outcomes, adjustment needs to be made for the clustered nature of the design. The inflation factor used to achieve this is determined from the average cluster size and the intra-cluster correlation (ICC) [42]. Empirical research has suggested ICCs of the order 0.10 for process measures and 0.05 for patient outcomes in primary care [43]. These have been used in the following calculations. It is estimated that 28% of current GP consultations for acute LBP in Australia result in a lumbar spine x-ray [7]. Interventions comparing standard CPG dissemination with no intervention control groups have shown improvements in care of approximately 8% [2]. We therefore anticipate a decrease in the percentage of x-ray prescription in the control group of this magnitude. We consider a reduction of 10% to be clinically important. Therefore, if the percentage of x-ray prescription at the end of the study in the control group is 20%, a sample size of 37 general practices per arm, with an average of 25 patients per practice, will be sufficient to detect an absolute decrease in the percentage of x-ray prescription of 10% (to 10%) or more with 90% power. This assumes a significance level of 5% and an ICC = 0.10.

This sample size will be sufficient to detect a clinically important difference of at least two points between groups in the RDQ with at least 99% power, assuming a standard deviation of six [44,45], significance level of 5%, and an ICC = 0.05.

Allowing for 20% attrition in practices (equivalent to 450 patient participants), we plan to initially recruit 46 practices per arm, with an average of 25 patients per practice, providing a total of 2,300 patients. These sample size calculations are likely to be conservative because, due to a lack of prior information, stratification has not been incorporated into the calculations.

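### The supplementary risk ratios, converted from covariate-adjusted odds ratios by a simple formula, will lie further from 1 than the population risk ratio; standardised risks from the same model avoid this at little cost

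*Protocol article*

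**What the plan says.** All of the following is in the protocol article, under Primary analysis unless another section is named.

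- Model: an exchangeable GEE with robust variance. "For binary outcomes, a logit link function will be used".
- Covariates: "Our primary analysis of outcomes will include adjustment for stratification variables (number of GPs per practice and rurality) and pre-specified potential confounders". The confounder list is in the full protocol, which is not shown. All listed confounders stay in the model whether or not the arms differ on them.
- Sensitivity: "estimates of intervention effect estimated from models including only the stratification variables will be presented".
- Effect measures: "Estimates of intervention effect from these models will yield odds ratios". To help interpretation, the authors will also "provide estimates of risk ratios using a simple formula that will utilise the odds ratios estimated from these models". The formula is cited but not printed.
- Intervals: "For each outcome, the estimate of intervention effect and its 95% confidence interval will be provided". How an interval for a converted risk ratio would be formed is not stated.
- Sample size section: the design has 37 practices per arm with 25 patients each and is "sufficient to detect an absolute decrease in the percentage of x-ray prescription of 10" percentage points, from 20% to 10%. That absolute reduction is also the difference called clinically important. The binary-outcome estimates named in the article are odds ratios and risk ratios.

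**The concern.** A GEE averages over practices, but its coefficient remains conditional on the covariates in the linear predictor. Odds ratios are non-collapsible: if a covariate predicts the outcome, the conditional odds ratio is further from 1 than the population odds ratio, even when the arms are perfectly balanced. A formula that combines the conditional odds ratio with a single overall control risk treats it as if it were the population odds ratio, so the risk ratio also comes out too far from 1. The article prefers GEEs partly because their coefficients describe the population and not one practice; the conversion loses part of that advantage.

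At stake is the supplementary risk ratio, which is the figure readers are most likely to find easy to quote. It would make a real benefit look somewhat larger than it is. A second question is whether its interval would have the right width.

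**Working it through.** **Inputs from the article.** Control risk 20%, intervention risk 10%, 37 practices per arm, 25 patients per practice, ICC 0.10, two-sided 5%, 90% power.

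**Assumptions.** The conversion has the usual form RR = OR / (1 − P0 + P0 × OR), with P0 the overall control risk. The covariate part of the linear predictor is normal with standard deviation s on the log-odds scale. The article gives no value for s, so a range is shown. Rates for advice to stay active are not given; 60 v 75% and 70 v 85% are assumed.

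**The plan's own figure.** The pooled two-proportion formula gives 266 patients per arm. The design effect is 1 + 24 × 0.10 = 3.4. Then 266 × 3.4 = 904.4, and 904.4 / 25 = 36.2, so 37 practices. The stated figure is reproduced.

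**Point estimate.** For each s, find intercepts a0 and a1 such that the average of expit(a + sZ) over a standard normal Z is 0.20 and 0.10. The conditional OR is exp(a1 − a0). Put it into the formula with P0 = 0.20. For s = 1.0: 0.4007 / (0.80 + 0.20 × 0.4007) = 0.4007 / 0.8801 = 0.455.

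| s | conditional OR | converted RR (true 0.500) | bias | implied reduction, 20 × (1 − RR) |
|---|---|---|---|---|
| 0 | 0.444 | 0.500 | 0% | 10.0 points |
| 0.2 | 0.443 | 0.498 | −0.4% | 10.0 |
| 0.5 | 0.433 | 0.489 | −2% | 10.2 |
| 1.0 | 0.401 | 0.455 | −9% | 10.9 |
| 1.3 | 0.374 | 0.428 | −14% | 11.4 |

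**Intervals, if the OR limits are put through the formula.** Take s = 0, to separate this from the bias above. The effective size per arm is n = 925 / 3.4 = 272. Write q = 1 − p. Then

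- var(log OR) = 1/(n p0 q0) + 1/(n p1 q1)
- var(log RR) = q0/(n p0) + q1/(n p1) by the delta method.

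With P0 held fixed, the slope of log RR on log OR is 1 − p1 = q1. The converted variance is therefore about q1²/(n p0 q0) + q1/(n p1). The second term is right. The control-arm term is multiplied by (q1/q0)², so the interval is too narrow when the intervention raises the outcome and slightly too wide when it lowers it.

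| Rates | (q1/q0)² | OR limits | converted RR limits | delta-method RR limits | log-width ratio |
|---|---|---|---|---|---|
| 20 v 10% | (0.90/0.80)² = 1.27 | 0.271–0.729 | 0.317–0.771 | 0.326–0.767 | 1.04 |
| 60 v 75% | (0.25/0.40)² = 0.39 | 1.387–2.885 | 1.126–1.354 | 1.110–1.408 | 0.78 |
| 70 v 85% | (0.15/0.30)² = 0.25 | 1.593–3.703 | 1.126–1.280 | 1.107–1.332 | 0.70 |

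In simulated beta-binomial trials (37 × 25 per arm, ICC 0.10), coverage of the converted nominal 95% interval is 95.0% at 20 v 10%, about 86% at 60 v 75% and about 81% at 70 v 85%. Delta-method intervals cover about 94% to 95% in all three.

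**The case against.** The case for leaving the plan alone has several sound parts.

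- **The risk ratio is an extra.** The models yield odds ratios, and the risk ratio is added for interpretability. A reader might infer that the trial's primary result is biased. It is not: the odds ratio, its robust interval and the test do not pass through the formula.
- **The bias may be trivial.** The confounders are deliberately few and their strength is unknown. An s of 0.5 corresponds to a c-statistic of about 0.64, and 1.0 to about 0.74. On the log scale the shift at s = 0.5 is ln(0.489/0.500) = −0.022, about 0.1 of the standard error of 0.219; at s = 1.0 it is −0.094, about 0.4 of it. The strata-only models are also presented, and if practice size and rurality predict weakly (s near 0.2) their conversion is almost exact.
- **The interval step is not in the article.** It does not say that odds-ratio limits will be converted with the control risk taken as known. A reader might infer that intervals will be too narrow in general, or for the primary outcome. Neither is supported: for x-ray referral the converted interval is about 4% wider on the log scale, and the shortfall appears only for common outcomes that the intervention raises, at rates assumed here.
- **A risk difference is not excluded.** A reader might infer that the absolute reduction will go unreported. The article is abridged and only does not name it. Sizing on an absolute difference and testing an odds ratio is not a contradiction.

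All of this stands, and it limits the point. It does not remove it: the article commits to deriving risk ratios from adjusted odds ratios by formula. The direction of the resulting bias is known under the usual form of that formula, and a better estimate comes from the same fitted model.

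**Conclusion.** The point holds for the supplementary risk ratios. With the usual formula and one overall control risk, a covariate-adjusted odds ratio gives a risk ratio further from 1 than the population value. At the design rates the error runs from negligible (0.498 for 0.500) to about 14% (0.428), depending on covariate strength that the article does not give.

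Under-coverage is conditional. It needs the unstated conversion of limits, a common outcome, and an effect that raises it; advice to stay active is the likely example. Sample size and primary inference stand. This is a cheap improvement to a secondary presentation, and does not call the trial's conclusion into question.

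**What to change.** Keep the logistic GEE for estimation and testing. Replace the conversion formula with standardisation: from the fitted model, predict every patient's risk under each arm, average within each arm setting, and contrast the two averages. Report both the risk ratio and the risk difference. The second is on the scale of the 10-point important difference and comes from the same two averages. Take intervals from the delta method with the robust covariance, or from a bootstrap that resamples practices.

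At the design rates with 37 × 25 per arm and ICC 0.10, and before any precision gain from covariates, this gives a risk ratio of 0.50 (95% interval about 0.33 to 0.77) and a risk difference of −10.0 points (about −15.9 to −4.1).

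The cost is a paragraph of analysis wording, entered as an amendment to the full protocol as the article already provides for, and a little more analysis work. No new data are needed and the sample size does not change.

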### Publication policy

The chief investigator will be responsible for ensuring timely production of a scientific manuscript at the completion of the trial. The results from the trial will be submitted for publication irrespective of outcome. All authors and the trial management committee, consisting of the authors listed on this publication, will review and approve the final manuscript prior to submission. The final trial results will be submitted for publication in a major international medical journal for wide dissemination. Reporting of this trial will adhere to the CONSORT statement and its extension to CRCTs [27,60]. Additional publications documenting development of the intervention, intervention fidelity and investigating mediating effects between primary and secondary outcomes are planned.

### Ethical review

Ethical approval for this trial was obtained from the Monash University Standing Committee on Ethics in Research involving Humans (2006/047). The investigators will ensure that the trial will be conducted in compliance with this protocol, the Guideline for Good Clinical Practice (CPMH/ICH/135/95) and the Australian National Statement on Ethical Conduct of Research Involving Humans.
